## Abstract

**Background:**

Sickle cell disease (SCD) is an inherited blood disorder that results in a lifetime of anemia, severe pain, and end-organ damage that can lead to premature mortality. While the SCD field has made major medical advances, much needs to be done to improve the quality of care for people with SCD. This study capitalizes on the Sickle Cell Disease Implementation Consortium (SCDIC), a consortium of eight academic sites aiming to test implementation strategies that could lead to more accelerated application of the NHLBI guidelines for treating SCD. This report documents the process to support the consortium by specifying the interventions being developed.

**Methods:**

This study consists of three steps. The Principal Investigator of each site and two site representatives who are knowledgeable of the intervention (e.g., study coordinator or the person delivering the intervention) will answer an online survey aiming to capture components of the interventions. This survey will be completed by the site representatives three times during the study: during the development of the interventions, after one year of the interventions being implemented, and at the end of this study (after 2 years). A site visit and semi-structured interview (Step 2) in the first year of the process will capture the context of the sites. Step 3 comprises of the development of a framework with the details of the multi-component SCDIC interventions at the sites.

**Discussion:**

The outcome of this study, a framework of the SCDIC, will enable accurate replication and extension of published research, facilitating the translation of SCD studies to diverse populations and settings and allowing for theory testing of the effects of the intervention components across studies in different contexts and for different populations.

**Trial registration:**

ClinicalTrial.Gov (#NCT03380351). Registered December 21, 2017.

## Background

Sickle cell disease (SCD) is an inherited blood disorder that results in a lifetime of anemia, severe pain, and end-organ damage that can lead to premature mortality [1]. SCD predominantly affects African Americans and other underrepresented minorities [2] and, while the field has made major medical advances [3], the average survival of African American individuals with SCD remains 30–45 years less than the average life expectancy for African Americans [4]. There are, however, efficacious interventions for SCD that can improve quality of life and life expectancy by reducing risks of stroke, pulmonary complications, need for transfusions, and reducing the number of pain episodes [5, 6]. Fortunately, the diagnosis of the disease is relatively simple, and mandatory newborn screening for SCD exists in all states so such interventions can be initiated early in the lifespan [7]. In 2014, the National Heart, Lung and Blood Institute released a set of evidence-based recommendations for treating SCD [8] but it is clear that the therapies proven to be efficacious are not reaching those in need [8, 9]. Implementation science, a field that aims to close the “quality gap” and support the transition of evidence-based intervention to usual care [10] can help improve the field of SCD care delivery [11].

Distinguishing between clinical studies and implementation studies may help clarify how implementation science can help improve the quality of care for people with SCD. Clinical studies aim to evaluate the efficacy or effectiveness of a specific intervention. Implementation studies, on the other hand, focus on *how* to successfully implement the intervention *in specific contexts* [12]. An implementation study aims to accelerate the adoption of an intervention or guideline by providers and/or systems of care, with the focus of the outcomes usually being at the provider and/or systems level [13]. In implementation studies, attention is given to the implementation strategies, defined as the processes by which evidence-based health innovations (e.g., audit and feedback, changes in the electronic record system, clinical supervision) are adopted and integrated into usual care [14]. These studies aim to change behaviors or settings at the organizational, practitioner, or patient level [15] with the goal of enhancing the adoption of an intervention or guideline. Implementation studies, therefore, require a paradigm shift [16] as they extend efficacy and effectiveness research focused on discovering *what* works to understanding *how* the implementation works *in specific contexts* [17].

The context of SCD care is complex and permeated with disparities. Treatment for SCD relies heavily on public insurance and healthcare programs [2], there are few specialized treatment centers [7], and the majority of people with SCD are minority and socioeconomically disadvantaged people who are also less likely than their counterparts to be linked to quality systems of care [18]. Children with SCD are at risk for life-threatening infections, strokes, acute chest syndrome, leg ulcers, pulmonary hypertension, among other complications [19]. Managing the disease involves multiple settings such as emergency department, as inpatient or outpatient, as well as at home and, for children, in school [20]. Proper management also includes both primary care and specialty care, though the latter may not always be available. Managing SCD is particularly complicated when adolescents are transitioning into adulthood, as they may have to move from a children’s clinic to adult clinics, adult emergency rooms, and hospitals. This may also be a time when individuals are taking on more responsibility for managing their own disease complications on their own, entering the workforce, and taking on other adult responsibilities [21].

### The sickle cell disease implementation consortium (SCDIC)

To address the challenges in managing SCD at this critical age juncture, the National Heart, Lung and Blood Institute (NHLBI), with co-sponsorship from the National Institute of Minority Health and Health Disparities, established a national research consortium to identify and test implementation strategies that could lead to more accelerated, consistent, and widespread application of the NHLBI guidelines. The Sickle Cell Disease Implementation Consortium (SCDIC): Using Implementation Science to Optimize Care of Adolescents and Adults with Sickle Cell Disease was established in 2016 [22] as a collaborative, multi-sector, research program that supports eight academic sites facilitated by a Data Coordinating Center – the Research Triangle Institute [11, 23]. The Consortium is charged with improving “the health and well-being of adolescents and adults with SCD in the US through the development of multi-modal, multi-sector interventions aimed at improving the rate at which patients with SCD receive routine primary care” [22].

Originally, each of the eight sites proposed a different intervention to achieve a common goal of improving the quality of care of people with SCD. To assist in cross-site collaboration, the SCDIC Executive Committee grouped site representatives from each of the eight academic sites to develop interventions in three main areas: (a) care redesign, (b) emergency department care, and (c) reducing the number of unaffiliated patients’ care. The specific research questions, designs and components of the interventions are currently being developed.

### Aims

The process described here was developed to support the sites in the SCDIC consortium by defining the components of the interventions with the goal of increasing the transparency and scientific reproducibility of the complex and multilevel studies being developed by the consortium sites.

### The importance of scientific reproducibility

One of the cornerstones of science is the ability to reproduce research findings [24]. In recent years, there has been a growing awareness of the need for transparency in studies to increase scientific reproducibility, including the launch of the clinicaltrials.gov in 2000, a registry where researchers record their methods and outcomes measures, and development of guidelines such as CONSORT [25], TIDier [26], and STaRI [27], to support transparency in research. Ideally these initiatives would facilitate replicability of major findings; however a number of studies have failed to replicate prominent findings or failed to achieve expected outcomes [28–31]. Insights from researchers reveal that, among other issues, the absence of clear descriptions of studies, including hypotheses for outcomes and descriptions of their interventions strategies [31, 32] make these studies virtually unusable, as they cannot be replicated, leading to inefficient use of research efforts and millions of dollars and efforts [33]. Unfortunately, the lack of detailed description of the interventions, including theoretical justification and review of the literature, is still prominent despite the push for publication guidelines [33, 34].

Describing components of complex interventions in the healthcare system, however, is challenging as often the relation between intervention, the implementation strategies and the contextual factors are dynamic, making the precise distinction among these components less clear [35]. A priori definition of the intervention components, the context, and the strategies used to implement the interventions can hopefully address many of the current problems in the intervention and implementation science fields: inconsistent labelling, disciplinary differences, vague descriptions (lack of transparency) and consequent difficult replication, and resultant inability to execute more precise meta-analyses [27, 35–40]. In other words, a standardized and detailed description of interventions allows accurate replication and extension of published research, facilitating the translation of studies to other populations and settings, allowing for theory testing of the effects of the intervention components across studies in different contexts and for different populations.

The description of a study needs to go beyond the correct and detailed description of methods and outcomes. A challenge to implementation research in any field is to capture what was proposed and what actually happened. There are at least two consequences of such mismatch and lack of transparency. First, by not adequately describing the study objective, methods, populations, interventions, outcomes measured and context, authors do not address, with high quality, their protocols in a proactive manner [33]. By proactively describing their studies in publications such as study protocols, researchers can contextualize their studies, allowing others to place their studies “into the context of totality of evidence” [41], and allowing others to reduce research waste by potentially doing similar studies when evidence has already been established. Second, it is well known that proposed studies differ from what actually happens when interventions are implemented [42, 43]. By clearly defining upfront the details of the interventions, and proactively defining what can be adapted, when and how adaptations can be made, it is hopefully easier to capture potential adaptations to the interventions once the study is ongoing [42]. In summary: “without accessible and usable report, research cannot help patients and their clinicians” [44].

To support the SCDIC, the process describe here aims to faciliatate the characterization of the interventions and strategies being developed by the SDIC in an effort to compare interventions. The primary outcome of this process will be a detailed framework of the SCDIC interventions that will support rigor and transparency, enable the Consortium to evaluate which intervention components were most effective in which settings, and will offer guidance to future efforts to improve treatment delivery and improve quality of life and life expectancy for adults living with SCD. This approach will also serve as a model for how other Consortia can describe, delineate, and evaluate interventions and implementation strategies across diverse sites.

## Methods

Guided by the recent report by the National Academy of Engineering (NAE) and the Institute of Medicine (IOM) calling for applying systems engineering methods to healthcare systems [45], we will focus on different levels that are interdependent and necessary to improve the quality of care. Accordingly, in the past years, approaches from the fields of engineering and business have been used to identify components of interventions [36, 46, 47] as predictors of outcomes [46, 48, 49]. This study is approved by the Washington University in St. Louis Human Research Protection Office (IRB Protocol # 201709005) and registered in the ClinicalTrial.Gov (#NCT03380351).

### Participants

Each site will have three representatives who will participate in this process: the PI of the study at that site and two people nominated by the PI as being the most knowledgeable of the intervention (e.g., study coordinator, interventionist/clinician). The interviews will be conducted in a half-day site visit. All data are being collected with the site representatives and there will be no contact with the patient participants of the SCDIC interventions. Because this study entails describing the interventions and how the interventions are delivered, the IRB has approved an information sheet to be provided to the site representatives instead of a written informed consent for the study.

### Data collection

The data collection for this study will have three phases: Step 1 will be a survey conducted prior to intervention implementation to capture the details of the proposed intervention. After one year, the survey will be conducted again, in addition to site visits (Step 2) to capture any differences between what was proposed and what is actually being implemented. Finally, Step 3 – which will take place on the second year 3 of this study, involves the sites’ representatives answering the survey again and developing a framework with detailed description of the SCDIC interventions.

#### Step 1: Developing the matrix

An online survey, adapted from a survey used in other consortia [50] will be developed to characterize the interventions. The survey, with multiple response options, will capture nine components of the interventions: (1) mode of delivery (e.g., face to face, video, phone), (2) materials used in the delivery of the intervention (e.g., manuals, pamphlets, videotapes), (3) where the intervention is being delivered (e.g., emergency department, primary care clinic, schools), (4) duration and intensity of the intervention (e.g., number of meetings, distribution of meetings over time), (5) scripting or how researchers or implementers plan to interact with providers and participants of the study (e.g., language provided to support interaction, general guidelines), (6) sensitivity to participant characteristics (e.g., visual supplements, oral supplements, literacy level); (7) interventionist characteristics (e.g., who is delivering the intervention, demographics of interventionist, how much training is required to deliver the intervention), (8) adaptability, or the extent to which an intervention can be modified (e.g., what, on what basis and when components can be modified), and (9) outcomes and hypothesis (i.e., planned outcomes being assessed, theoretical rationale for the outcomes, hypothesis being tested; when, and who will conduct the assessments).

To capture the implementation strategies, the survey will also incorporate recommendations on specifying and reporting implementation strategies [36] by asking the research teams to identify (a) who is delivering the intervention, (b) what are the actions, (c) who is the action target, (d) the temporality (i.e., when the strategy is being used), (e) the dose (i.e., how often the strategy is being used), (f) the implementation outcome likely affected by the strategy, and (g) the theoretical justification for using the strategy.

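### The first implementation-strategy survey item asks who delivers the intervention, so it repeats component 7 and no listed item asks who enacts the strategy

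*Protocol article*

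**What the plan says.** Under *Step 1: Developing the matrix*, the protocol article describes an online survey in two parts.

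The first part covers nine components of the interventions. The seventh reads "7) interventionist characteristics (e.g., who is delivering the intervention, demographics of interventionist, how much training is required to deliver the intervention".

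The second part has a different object: "To capture the implementation strategies, the survey will also incorporate recommendations on specifying and reporting implementation strategies". Its seven items start with "by asking the research teams to identify (a) who is delivering the intervention, (b) what are the actions, (c) who is the action target" and go on to "d) the temporality (i.e., when the strategy is being used), (e) the dose (i.e., how often the strategy is being used". The last two, (f) and (g), ask for the implementation outcome the strategy is likely to affect and the theoretical reason for using it.

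Elsewhere the article keeps the two objects apart. *Background* says that in implementation studies "attention is given to the implementation strategies, defined as the processes by which evidence-based health innovations" are taken up into usual care, with audit and feedback, electronic record changes and clinical supervision among its examples. *The importance of scientific reproducibility* calls for "A priori definition of the intervention components, the context, and the strategies used to implement the interventions", naming these as separate things to define.

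**The concern.** A set of items introduced as describing the strategy opens with a question about the intervention. Taken as written, item (a) collects again what component 7 collects, and the place where one would expect the strategy's actor is filled by something else.

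This matters more here than in an ordinary trial because the description is the result. The article names the framework of the interventions as the primary outcome and gives inconsistent labelling and vague description as the problems to be solved. The *Discussion* adds that hematologists and implementation scientists use the word implementation differently. The respondents are the site PI and two people chosen for their knowledge of the intervention, so a question worded around the intervention is likely to be answered about the intervention. At a site where, say, an informatics team changes the record system and a nurse delivers the intervention, the nurse would be recorded twice and the informatics team would be missed.

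**Working it through.** The point concerns wording, so there is no figure to reproduce. The check is to compare the two lists and then look for the strategy's actor anywhere else.

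**Step 1: the object of each strategy item.**

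| Item | Asks about | Object named |
|---|---|---|
| (a) | the person delivering | the intervention |
| (b) | actions | none |
| (c) | target of the action | none |
| (d) | timing | the strategy |
| (e) | dose | the strategy |
| (f) | implementation outcome affected | the strategy |
| (g) | theoretical justification | the strategy |

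Item (a) is the only one of the seven that names the intervention. Four name the strategy, and two name neither.

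**Step 2: overlap with the intervention list.** Component 7 includes "interventionist characteristics (e.g., who is delivering the intervention, demographics of interventionist". The phrase used for the deliverer is identical to that in item (a), so the two ask for the same information.

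**Step 3: is the strategy's actor requested by another item?** There are 9 + 7 = 16 listed items. Those that concern people are:

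- component 5, on how researchers or implementers plan to interact with providers and participants. It concerns the manner of interaction and does not ask who enacts a strategy;
- component 6, on participant characteristics;
- component 7, on the interventionist;
- component 9, which includes "when, and who will conduct the assessments". That is the assessor;
- item (a), the deliverer of the intervention;
- item (c), the target of the action, which is the receiving end.

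The other items concern mode, materials, place, duration, adaptability, actions, timing, dose, outcome and justification. None of the 16 asks who enacts the strategy.

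**Step 4: is it requested in a later step?** *Step 2* repeats the survey, adds a half-day visit to learn about context, and allows follow-up calls if needed to complete the matrix. *Step 3* repeats the survey and shows the framework to the sites in a webinar for comment on accuracy. Any of these could bring the actor to light, but none is stated to record it.

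**Step 5: when does the gap bite?** If the same people deliver the intervention and enact the strategy, the answer to item (a) happens to be the wanted one. Information is lost only where they differ. The *Background* examples show that they can differ, but the document does not say at how many sites they do.

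**The case against.** The strongest reply is that the article summarises topics for a survey that is yet to be developed. The questionnaire is not shown, and it is to follow a cited recommendation on specifying strategies. The sentence opens by naming strategies as its subject, so item (a) may be only a slip of wording that the instrument itself will not carry. That is a fair account of how the text may have arisen. It limits how much harm can be claimed, but it does not remove the mismatch. The article does not leave the item out; it states the item with the wrong object.

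A second reply is that the article's own terms overlap. It says the consortium will test implementation strategies, yet calls what the sites develop interventions, and it concedes that the boundary is hard to draw in complex care. Where a site's intervention is itself the strategy for guideline uptake, item (a) does identify the actor. This stands for such sites. It does not cover sites where the two differ, and a blurred boundary is a reason for clearer wording.

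A third reply is that the answer to (b), the site visits, the calls or the webinar could supply the actor. They could, although nothing commits them to it. A reader might infer that the actor would never be recorded, could not be recovered for the Step 1 baseline, or that strategies could not be replicated or compared across sites. The document does not support these stronger readings, because those other routes remain open.

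**Conclusion.** The point holds as a wording fault in the survey specification. Item (a) duplicates part of component 7, does not match items (d) to (g), and leaves the strategy's actor unasked in all 16 listed items. The consequence is conditional: the framework would lack the actor for strategies enacted by people other than the interventionist, unless another route happened to capture it.

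This rests on two assumptions: that the instrument follows the list as printed, and that at some sites the two groups of people differ. The document confirms neither.

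The size cannot be put as a rate. A reader might express it as one of seven strategy items, or multiply eight sites by three respondents by three survey rounds. The first is a share of a list and the second is the planned number of survey completions. Neither counts records that would actually lose information. It is also tempting to conclude that items (a) to (g) must be completed separately for each strategy, but the article does not say that they are completed only once per site, so no defect is shown there.

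**What to change.** Before the Step 1 survey is launched, reword item (a) to ask who enacts or delivers the implementation strategy, in line with items (d) to (g). Keep the question of who delivers the intervention in component 7 only. If the instrument already asks about the strategy's actor, only the article's description needs correcting.

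The cost is one reworded item. The number of items is unchanged, and the planned steps and analysis are not affected.
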